#### Main study

Our primary hypothesis is that, after 27 months, we will observe a clinically important and statistically significant increase in lumbar spine BMD, expressed in percent change from baseline, among women randomized to treatment compared with placebo. Our sample size calculation is based on t-test and will allow us to detect a 2% difference in spine BMD; 2% is the minimal difference that would justify nitrate treatment as this is the minimal magnitude of BMD change observed with other accepted osteoporosis treatments [5,61,62,78,79]. The standard deviation of change with a 2% difference in BMD ranges from 4.5% to 6.8% [5,59,62,80,81]. Assuming a standard deviation of change of 4.5%, a two sided alpha of 0.05 and a power of 0.90 we require 107 subjects per group [81].

The main trial will be preceded by a nitrate run-in phase and only women who complete the run-in phase will be entered into the main trial (see section 2.1aii). Our previous data indicate that 16 of 96 (17%) women randomized to ISMO dropped out due to headaches and 6 of the 144 (4%) women did not return to the study centre after randomization and were lost to follow up [42]. Thus we will "over recruit" by 25% to allow for a 17% drop out in the run-in phase due to headaches and a 8% loss to follow up during the main trial. Thus, we will recruit 280 subjects of whom we anticipate that 232 subjects will complete the run-in phase and enter the main trial (116 subjects per group). This sample size will ensure that we observe a clinically important and statistically significant difference between the active treatment and placebo group. Our sample size gives us adequate power to test our secondary hypotheses (Table 4B).

**Table 4B T5:** Required sample size to test all secondary hypotheses in main study.

Hypothesis	Clinically Important Difference	Standard Deviation of Change	Subjects, per group
Hip BMD will be higher in treatment group*	2%	4.5% (5, 59, 62, 80, 81)	107
NTx will lower in treatment group†	15% (69, 87–89)	28% (30, 35)	105
BSAP will be higher in treatment group†	15% (69, 87–89)	25% (30)	105
Headaches due to nitrates will be higher in treatment group**	20% (30)	5% (30)	36
Trabecular bone density by pQCT will be higher in treatment group**	10 mg/cm^3 ^(67, 70)	7.5 mg/cm^3 ^(67, 70)	31

* Based on a t-test, assuming a two sided alpha of 0.05 a power of 0.90 and a standard deviation of change in BMD measurements of 4.5%.

† Assuming a repeated measures analysis of variance (75).

** Based on a Student's t test, assuming a two sided alpha of 0.05, a power of 0.90.

The estimated 17% drop out rate from headaches in the run-in phase is conservative as the pilot study will identify the best tolerated nitrate. We anticipate that less than 1% of women will drop out from headaches during our main trial based on the fact that in our earlier trial the majority of the women who dropped out due to headaches did so within the first 48 hours.

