Hip BMD		
Unadjusted	0 (-2.7 to 1.4)	0 (-4.1 to 4.1)
Adjusted*	1.3 (0.14 to 4.1)	2.6 (0.4 to 6.8)
		
Heel BMD		
Unadjusted	-2.6 (-5.3 to 0)	0 (-5.3 to 7.9)
Adjusted*	0 (-2.6 to 2.6)	5.3 (2.6 to 11)

*Adjusted for estrogen use and baseline differences (37), which are current alcohol intake, walks for exercise, physical activity, self-reported health status, falls in the past 12 months, thiazide and nonthiazide diuretic use, inability to rise from a chair independently and frail on physical examination.

There are two potential explanations as to why intermittent nitrate use associated with greater BMD than continuous use. First, women who use nitrates intermittently may have better health and fewer risk factors for low BMD than women who require continuous nitrates. However, adjusting for known for differences in health status did not mitigate the nitrate effect. Second, the findings may be due to chance variation. However the results were robust and statistically significant when we examined BMD at both the hip and the heel.

The average dose of nitrate among women reporting intermittent use was 0.2 mg/day of NTG. This is well below the doses required for angina treatment: a typical single dose is 0.3 mg and daily doses range from 0.3 mg to 0.9 mg. Among the 74 women reporting intermittent use, the type (ISMO, isosorbide dinitrate and NTG), the form (sublingual tablet or spray, oral tablets, sustained release tablets, transdermal patch or ointment), and the dose varied. This suggests an intriguing possibility that nitrates of any type administered intermittently in low doses can increase BMD.

The next step in our program of research was a RCT comparing the effects of placebo and intermittent ISMO on markers of bone turnover in postmenopausal women. We randomly assigned 144 women (≥ 3 years postmenopausal with femoral neck BMD T-scores between 0 and -2.5) to 12 weeks of placebo or intermittent ISMO of 5 mg or 20 mg per day; typically ISMO is prescribed at 20 mg twice a day. We measured changes from baseline in urine N-Telopeptide (NTx), a marker of bone resorption and serum Bone Specific Alkaline Phosphatase (BSAP), a marker of bone formation [30,31].

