We found that, compared with placebo, women randomized to intermittent ISMO at 20 mg had a 45.4% decrease in NTx (95% confidence interval [CI]: 25.8 to 64.9) and a 23.3% increase (95% CI: 8.9 to 37.8) in BSAP. Women randomized to intermittent ISMO at 5 mg had a 36.3% decrease in NTx (95% CI: 14.8 to 57.8) and a 15.9% increase in BSAP (95% CI: 1.1 to 30.7) (Figure 2) [30,31]. The decreases in NTx observed with 20 mg of ISMO are similar to those reported with alendronate, risedronate, and estrogen (about 50%) and greater than the 25% decreases reported with raloxifene [40,41]. However, all of the antiresorptive agents concomitantly decrease rates of bone formation. In contrast, we observed that treatment with ISMO resulted in significant increases in BSAP. The decrease in resorption, coupled with the increase in formation, suggests that ISMO may reduce fracture risk to an even greater degree than that seen with the current antiresorptive agents. The only adverse event was headache. Headaches, were more common among women randomized to ISMO (5 and 20 mg groups combined n = 55, 57%) compared with placebo (n = 2, 4%; p = 0.004). Headaches were no more common among women taking 20 mg of ISMO (n = 28) than among women taking 5 mg of ISMO (n = 27; p = 0.7).

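### Table 4B's marker rows use SDs well below those implied by the protocol's own earlier trial, so adequate power is not supported for a 15% NTx difference

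*Protocol article*

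**What the plan says.** Section 2.5 (Main study) states for the primary outcome: "Assuming a standard deviation of change of 4.5%, a two sided alpha of 0.05 and a power of 0.90 we require 107 subjects per group". It expects that "232 subjects will complete the run-in phase and enter the main trial (116 subjects per group"), with an 8% loss to follow-up during the trial. It then says "Our sample size gives us adequate power to test our secondary hypotheses" and refers to Table 4B.

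Two rows of that table concern bone turnover markers:

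- "NTx will lower in treatment group": difference 15%, SD of change 28% (references 30 and 35), 105 per group.
- "BSAP will be higher in treatment group": difference 15%, SD of change 25% (reference 30), 105 per group.

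The footnote to these two rows reads "Assuming a repeated measures analysis of variance (75") and gives no alpha, power or within-subject correlation. The footnotes to the other rows state two-sided 0.05 and power 0.90.

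Reference 30 is one of the two references given for the earlier isosorbide trial in section 1.4 ("We randomly assigned 144 women"). For 20 mg against placebo it found a "45.4% decrease in NTx (95% confidence interval [CI]: 25.8 to 64.9"). The same section gives intervals for NTx at 5 mg (14.8 to 57.8), BSAP at 20 mg (8.9 to 37.8) and BSAP at 5 mg (1.1 to 30.7).

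**The concern.** An interval for a difference between two arms, together with the arm sizes, fixes the SD approximately. The intervals in section 1.4 are much too wide for SDs of 28% and 25% in arms of about 48 women. The two rows also share one difference and one sample size while their SDs differ, which the stated inputs do not explain.

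At stake is how far the marker results can be relied on at the difference the plan itself calls clinically important. Section 2.4 uses the 12- and 24-month markers to ask whether the nitrate effect persists. An effect that has weakened towards 15% is where a shortfall in NTx power would matter.

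**Working it through.** **Inputs.** Differences, SDs and group sizes come from section 2.5 and Table 4B. The intervals come from section 1.4. The earlier trial's size comes from sections 1.4 and 2.1.2: 96 women on isosorbide in two dose arms and 48 on placebo, with 16 and 2 headache dropouts. Section 2.5 adds 6 of 144 lost to follow-up. After 8% loss, 116 per group becomes 116 × 0.92 ≈ 107.

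**1. Reproducing the plan's figures.** n per group = 2(1.96 + 1.282)²(SD/difference)².

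- Primary: 2 × 10.51 × (4.5/2)² = 106.4, so 107. This reproduces.
- NTx: 2 × 10.51 × (28/15)² = 73.2, so 74. The table says 105.
- BSAP: 2 × 10.51 × (25/15)² = 58.4, so 59. The table says 105.

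At this alpha and power, 105 per group corresponds to an SD of 33.5%.

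**2. SDs implied by the earlier trial.** SE = (upper − lower)/3.92, and SD = SE/√(1/n₁ + 1/n₂). Three assumed pairs of arm sizes (isosorbide/placebo) are shown: as randomized with equal isosorbide arms (48/48), headache dropouts removed (40/46), and two more lost per arm (38/44).

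| Interval | Half-width | SE | SD 48/48 | SD 40/46 | SD 38/44 |
|---|---|---|---|---|---|
| NTx 20 mg | 19.55 | 9.97 | 48.9 | 46.1 | 45.0 |
| NTx 5 mg | 21.5 | 10.97 | 53.7 | 50.7 | 49.5 |
| BSAP 20 mg | 14.45 | 7.37 | 36.1 | 34.1 | 33.3 |
| BSAP 5 mg | 14.8 | 7.55 | 37.0 | 34.9 | 34.1 |

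Conversely, with 48 per arm an SD of 28% would give an NTx half-width of 1.96 × 28 × √(2/48) = 11.2, and an SD of 25% a BSAP half-width of 10.0. For the table's SDs to produce the quoted intervals, the earlier trial would have needed only about 13–16 women per arm (NTx) or 22–23 (BSAP).

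**3. Power for a 15% difference, one visit.** Power ≈ Φ(15/(SD√(2/n)) − 1.96). For NTx with 107 per group:

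- SD 53.7: 15/7.34 − 1.96 = 0.08, power 53%.
- SD 45.0: 15/6.15 − 1.96 = 0.48, power 68%.

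With 116 per group the range is 56–71%. Reaching 90% would take 190–270 per group by the step 1 formula. Ranges here and in step 4 use the t distribution, which is at most about half a point lower than the normal formula. BSAP with 107 per group has 84–91%.

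**4. Averaging the 3-, 12- and 24-month visits.** The variance is multiplied by (1 + 2ρ)/3, which is 0.667 at ρ = 0.5 and 0.80 at ρ = 0.7 (both assumed). With 107 per group:

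- NTx: from 62% (SD 53.7, ρ = 0.7) to 84% (SD 45.0, ρ = 0.5).
- BSAP: 91% or more.

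NTx reaches 90% only if ρ is at most about 0.10 (SD 53.7) to 0.35 (SD 45.0). Percent changes from one shared baseline carry its error in common, so correlations that low are unlikely.

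**5. Larger effects.** At differences of 36.3 and 45.4 points, the earlier NTx estimates, power with 107 per group exceeds 99% even at SD 53.7.

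**The case against.** The other side has several good points.

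- **No power is stated for the marker rows.** A reader might infer a 90% claim from the rest of the table, but the marker footnote gives none and the text says only that power is adequate. This stands, so 90% serves here as the benchmark used elsewhere, not as a figure the plan gives for NTx.
- **The NTx SD has two sources.** It also cites reference 35, which is not available here. Only the BSAP row is a same-source conflict, and BSAP has no material power problem. This stands, but the combined 28% is still far below what the protocol's own trial implies.
- **Equal sizes for unequal SDs are not impossible.** A reader might call them so. Repeated-measures sample size depends on the contrast and the correlation, and neither is stated. Averaging visits lowers n, but a contrast of change between two visits multiplies the variance by 2(1 − ρ). The required factors, 105/73.2 = 1.43 and 105/58.4 = 1.80, would follow from ρ of about 0.28 and 0.10. The figure is unexplained and, on the table's own SDs, larger than a t-test needs.
- **A null result could still exclude 15%.** A reader might infer the opposite from the low power. With 107 per group at one visit, the 95% half-width would be 1.96 × SD × √(2/107), or 12.1 to 14.4 points at SD 45.0 to 53.7. An estimate near zero would therefore exclude 15%.
- **The SD may not carry over.** The main trial adds a calcium and vitamin D phase before the marker baseline and analyses stored samples together, which could reduce variability. The protocol does not quantify this. For 90% power at one visit with 107 per group, the NTx SD would have to fall to about 34%.
- **Practical weight is limited.** NTx is a secondary outcome, and an averaged analysis with favourable assumptions reaches power some would call adequate.

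**Conclusion.** The marker rows of Table 4B need correcting. Their SDs are below those implied by section 1.4 by a factor of about 1.6–1.9 for NTx (45–54% against 28%) and 1.3–1.5 for BSAP (33–37% against 25%). The 105 per group is not reproduced for either marker from the stated inputs.

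The consequence is material only for NTx at the stated 15% difference. There, adequate power is not supported at the 90% level used elsewhere in the section. This rests on equal isosorbide arms, 38–48 women per arm in the intervals, the earlier SD carrying over to the main trial, and the assumed correlations for the averaged analysis.

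The documents do not support extending this to BSAP, to NTx effects of 36–45%, or to the primary outcome, whose sample size reproduces.

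**What to change.** - Reconcile the 28% and 25% SDs with the intervals in section 1.4. If another source justifies a smaller NTx SD, say which and why.
- Recompute both marker rows, stating alpha, power, the contrast tested (one visit, average of visits, or change between visits) and the assumed correlation.
- In place of the general statement of adequate power, give the NTx power for 15% or the detectable difference. With 107 per group, one visit and 90% power, the latter is about 20–24 points for SDs of 45.0–53.7%.

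The cost is a corrected table and a reworded sentence, with no more women or samples. Analysing log marker ratios with the baseline log marker as covariate is an optional way to recover precision. Its gain has not been calculated here, it changes the quantity estimated, and it does not replace correcting the table.

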## 3.0 Discussion

We successfully completed our pilot study in August 2005. We found that headaches were significantly lower when women were randomized to nitroglycerin ointment compared with oral isosorbide mononitrate. As a result, the main study is assessing the effects of nitroglycerin ointment on bone mineral density. To date, we have screened 310 subjects, 77 have entered the one week nitrate run in phase, 25 women dropped out after the one week nitrate run-in phase (19 of these due to headaches) have dropped out and 52 women are still participating in the trial.

Nitrates have several advantages over the medications currently used to prevent and treat OP. Unlike ERT, there have been no reports of an increased risk of cardiovascular disease or breast cancer with long-term use of nitrates [43-46]. Compared with bisphosphonates and raloxifene, nitrates are generally more available world wide, more convenient to take, and less expensive. Clearly, further studies of nitrates are essential.

The value of nitrates for prevention of fracture will require a randomized blinded trial with a fracture outcome. We plan to conduct an international trial comparing intermittent nitrates with standard pharmacologic therapy to prevent fractures in women with OP. Prior to the RCT, we must determine the form of nitrate that is associated with the least severe headaches and also determine if intermittent nitrates can increase spine BMD. These are the main objectives of this trial.

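### The 17% run-in headache loss is called conservative, but early run-in data on the chosen nitrate run higher, so 280 entrants are not shown to give 232 women or 90% power

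*Protocol article*

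**What the plan says.** Section 2.5 (Main study) sets the requirement: "Assuming a standard deviation of change of 4.5%, a two sided alpha of 0.05 and a power of 0.90 we require 107 subjects per group", for a 2% difference in percent change of spine BMD. The recruitment figure adds an allowance "to allow for a 17% drop out in the run-in phase due to headaches and a 8% loss to follow up during the main trial", so that "we will recruit 280 subjects of whom we anticipate that 232 subjects will complete the run-in phase and enter the main trial", or 116 per group. Section 2.1 gives the same run-in loss as a count, 48 of 280.

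The 17% comes from the earlier trial of oral isosorbide mononitrate: "16 of 96 (17%) women randomized to ISMO dropped out due to headaches". The notes under Table 4B then say "The estimated 17% drop out rate from headaches in the run-in phase is conservative", on the ground that the pilot will have identified the better tolerated preparation.

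Section 3.0 reports that the pilot is complete, that nitroglycerin ointment was better tolerated, and that the main study uses it. Of 77 women who had entered the run-in, "25 women dropped out after the one week nitrate run-in phase (19 of these due to headaches", and 52 remained in the trial. The article does not revise 17%, 280 or 232 in the light of this.

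**The concern.** The reason given for calling 17% conservative is that the better tolerated nitrate would be used. The women counted in section 3.0 were already on that nitrate, and their loss is above 17%, whether counted for headache alone or in total. The step from 280 to 232 removes only the 17%, so it has no room for a higher headache rate or for run-in losses for other reasons.

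At stake are the stated size and the 90% power for the primary comparison. Table 4B also asks for 107, 105 and 105 per group for hip BMD, NTx and BSAP, so the claim of adequate power for those outcomes depends on the same yield.

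**Working it through.** **Inputs.** From section 2.5: difference 2%, SD 4.5%, two-sided alpha 0.05, power 0.90, run-in loss 17%, later loss 8%, 280 recruited, 232 entering. From section 3.0: 77 run-in entrants, 25 lost, 19 of them for headache, 52 remaining.

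**The plan's own figures reproduce.**
- Per group: n = 2 × SD² × (1.960 + 1.282)² / difference² = 2 × 20.25 × 10.51 / 4 = 106.4, rounded up to 107.
- Recruited: 214 / (0.83 × 0.92) = 280.3.
- Entering: 280 × 0.83 = 232.4. Evaluable: 232 × 0.92 = 213.4, about 107 per group.
- Whole planned attrition: 1 − 0.83 × 0.92 = 23.6%.

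**Observed loss, with exact binomial 95% intervals.**
- Headache only: 19/77 = 24.7% (15.6% to 35.8%). Against 17%, p = 0.09.
- All causes: 25/77 = 32.5% (22.2% to 44.1%).

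**Consequence for 280 entrants.** Entering = 280 × (1 − run-in loss). Evaluable per group = entering × 0.92 / 2. Power is from the two-sample t-test with difference 2% and SD 4.5%.

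| Run-in loss used | Entering | Evaluable per group | Power | Entrants needed for 232 |
|---|---|---|---|---|
| 17% (plan) | 232 | 107 | 90% | 280 |
| 24.7% (headache only) | 211 | 97 | 87% | 308 |
| 32.5% (all causes) | 189 | 87 | 83% | 344 |

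The last column is 232 / (1 − run-in loss): 232/0.753 = 308 and 232/0.675 = 344.

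**Between the two observed rows.** Suppose all 25 losses are counted and nobody else is ever lost. Then 280 × 52/77 = 189 remain, or 94.5 per group, and power is 86%. Suppose instead that the six non-headache losses all belong to the main trial. They are then 6 of the 58 who entered it (77 − 19), or 10.3%, already above the 8% allowed, though on very small numbers. The 87% row therefore relies on the 8% holding.

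**Spread from having only 77 women.** These figures use the interval limits, still with 8% later loss.
- Headache only, 15.6% to 35.8%: 236 to 180 entering, 109 to 83 per group, power 90% to 81%, and 275 to 362 entrants needed.
- All causes, 22.2% to 44.1%: 218 to 157 entering, 100 to 72 per group, power 88% to 75%, and 299 to 415 entrants needed.

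**Dependence on the SD.** All of this uses 4.5%, the low end of the article's own range: "The standard deviation of change with a 2% difference in BMD ranges from 4.5% to 6.8". At 6.8%, 107 per group gives about 57% power and 87 per group about 49%. That is a separate matter from the run-in, but it means the SD leaves no margin to absorb the loss.

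**The case against.** **Like for like.** A reader might infer that the article disproves its 17% with an observed 32%; an exact test of 25/77 against 17% gives p = 0.001. That sets all-cause loss against an assumption about headache only. The matching figure is 24.7%, and its interval includes 17%. This stands: the early data fail to support the word conservative, but they do not refute 17% as a headache rate.

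**Which allowance the six other losses belong to.** Section 3.0 places the drop-outs after the one-week run-in. Sections 2.1.2 and 2.2 place the three-month calcium and vitamin D phase inside the main trial, where the 8% applies. Some or all of the six may therefore already be budgeted, and taking 32.5% and then a further 8% may count them twice. This also stands, and it makes 87 per group and 83% the pessimistic end. Against the whole planned attrition of 23.6%, the interval for 25/77 (22.2% to 44.1%) includes the plan.

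**What 232 is.** It might be read as the number randomised, so that the trial would randomise 189 instead of 232. The article gives 232 as the number entering the main trial; randomisation follows three months later among those who return.

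**Whether the trial must end up short.** Run-in loss comes before randomisation, does not bias the comparison, and can be made up with more entrants. The article does not say that recruitment stops at 280 if fewer than 232 enter. This stands too: the shortfall is conditional on keeping 280.

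The objection does not rescue the word conservative or the unrevised yield. The stated reason for caution was already in force, and both point estimates are above 17%.

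**Conclusion.** The point holds in a limited form. The 17% cannot be called conservative on the article's own data, and 280 run-in entrants are not shown to deliver 232 women entering the main trial. On the point estimates, with the planned 8% later loss, 280 entrants give about 189 to 211 entering, 87 to 97 evaluable per group and 83% to 87% power. With all 25 losses counted and none afterwards, power is 86%. Each of these readings is below the stated 90%.

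This rests on a 2% difference, an SD of 4.5%, early rates from 77 women that persist, and recruitment held at 280. The most favourable limit for headache loss (15.6%) would still meet the plan. The power loss is moderate and recoverable. It is a fault in the stated size and power, and it leaves the validity of the comparison intact.

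**What to change.** In sections 2.1 and 2.5, including the notes under Table 4B, delete the word conservative. Keep the original 17% with its source, so that the planning rationale stays visible, and report beside it the observed run-in loss: 19/77 for headache and 25/77 in all, with intervals. State in which phase the six non-headache losses occurred; that settles which end of the range applies.

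Then do one of two things:
- Keep 280 and restate what it is expected to give: about 189 to 211 women entering the main trial, 87 to 97 evaluable per group and 83% to 87% power at SD 4.5%.
- State that 232 entering the main trial is the target, and that about 308 to 344 run-in entrants are expected to be needed, with the wider range that 77 women imply.

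The first costs only a revision of the text. The second adds about 28 to 64 run-in entrants (308 − 280 and 344 − 280). Run-in loss precedes randomisation and shows nothing about the treatment comparison, so updating it during recruitment has no type I error cost and needs no interim analysis.
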